### Safety monitoring

All adverse events from consent through hospital discharge–neurological deterioration, unplanned neurosurgical intervention, escalation of care, or death–are recorded prospectively; serious AEs (death, life-threatening event, or event resulting in prolonged hospitalization) are reported to the IRB and sponsor within 24 h. A blinded investigator adjudicates event relatedness to study procedures. An independent Medical Monitor reviews cumulative safety data quarterly and at each interim analysis, with authority to recommend protocol modifications or early termination if predefined neurologic severe adverse events thresholds are exceeded (Table 3).

**Table 3 tab3:** SPIRIT guidelines.

Timepoint	Study period				
	Enrolment	Allocation	Post-allocation	Follow up	Close-out
	t1	t2	t3	t4	t5
Enrolment					
Eligibility screen	X				
Informed consent	X				
Baseline assessment (GCS, labs)	X				
Randomization		X			
Interventions					
Biomarker testing		X	X		
Biomarker result communicated		X (if applicable)	X		
Standard care			X		
Assessments					
Head CT (if performed)			X		
Length of stay			X		
Adverse events monitoring			X		
Outcome adjudication (blinded)			X		
6 months follow-up (phone)				X	
12 months follow-up (phone)					X

GCS, Glasgow Coma Scale; Labs, Laboratories; CT, computed tomography.

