## Methods and analysis

### Study objective

The BRAIN-CT trial investigates whether providing emergency-department clinicians with rapid GFAP and UCH-L1 results, via the point-of-care i-STAT TBI cartridge, changes imaging behavior in adults with mild traumatic brain injury. The primary objective (Table 2) is to compare the proportion of patients who receive a head CT scan between a biomarker-published arm and a standard-care (biomarker-blinded) arm; we hypothesize that real-time access to GFAP and UCH-L1 levels will lower the CT scan rate compared with standard management. To address this objective, we have designed a prospective, randomized, open-label, blinded-endpoint (PROBE) adaptive trial that will enroll 350 participants, randomized 1:1 to biomarker-published versus biomarker-blinded arms using permuted blocks stratified by age group, biological sex, race, and baseline Canadian CT Head Rule risk category (Supplementary Table 1). Frequent interim analyses with prespecified efficacy and futility boundaries will permit early stopping if criteria are met.

**Table 2 tab2:** Primary and secondary objectives of the BRAIN-CT trial.

Objective	Category	Objective description	Outcome measured
Primary	–	Evaluate whether real-time access to point-of-care TBI biomarker results (GFAP, UCH-L1) reduces the use of cranial CT imaging.	Proportion of patients undergoing head CT.
Secondary (clinical impact) two-arm comparisons	Clinical decision-making	Assess the impact of biomarker result access on physician decision-making for CT use.	CT imaging timing and provider rationale.
	Efficiency and cost	Determine whether biomarker use reduces ED/hospital length of stay and healthcare costs.	LOS, resource use, hospital charges. Perform a formal ICEA of biomarker testing versus standard care.
	Patient outcomes	Compare short-term outcomes between arms (neurological deterioration, readmissions, GOS, GCS).	GOS-E/GCS at 6 months and 1-year follow-up, neurological symptoms.
	Radiation exposure	Quantify radiation dose reduction per patient between arms.	Directly measure a key safety benefit.
	Disparity analysis	Identify patient subgroups (e.g., by age, injury mechanism, comorbidity) where biomarkers influence decision-making.	Stratified CT usage, subgroup analysis of impact.
	Safety monitoring	Monitor for adverse outcomes from missed injuries in biomarker-guided arm.	Adverse events, unexpected deterioration, delayed diagnoses.

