### Post-randomization in-hospital assessment

After allocation, participants are followed throughout their ED stay and – if admitted– for the duration of hospitalization. Study coordinators prospectively capture whether a head-CT is performed, its timing and radiology results; emergency-department and inpatient length of stay; any neurological deterioration or other adverse events; and final disposition or admission status.

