### Post-discharge follow-up

Study staff will conduct structured telephone interviews at 6 months and 12 months after the ED visit to ascertain persistent or late-presenting neurologic symptoms, unplanned healthcare utilization (ED visits, hospital readmissions, outpatient imaging), and any delayed diagnoses of intracranial injury. Future contact is approved by subjects at the time of consent. When participants cannot be reached after three call attempts, electronic health-record review and contact of designated surrogates are attempted to complete the data set. Designated surrogates are individuals determined by the subject to be their emergency contact for the study for future contact and are named at the time of informed consent.

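### Adverse event recording stops at hospital discharge and the next contact is at 6 months, so a delayed diagnosis in a patient sent home unscanned falls outside expedited reporting and reaches the Medical Monitor late

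*Protocol article*

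**What the plan says.** All references are to the protocol article.

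- **Recording window.** Safety monitoring covers "All adverse events from consent through hospital discharge". Post-randomization in-hospital assessment agrees: "participants are followed throughout their ED stay" and, if admitted, through the admission. In Table 3 the row "Adverse events monitoring" is marked at t3 only, not at t4 (6 months) or t5 (12 months).
- **Expedited reporting.** In the same Safety monitoring sentence, "serious AEs (death, life-threatening event, or event resulting in prolonged hospitalization) are reported to the IRB and sponsor within 24 h".
- **After discharge.** Under Post-discharge follow-up, "Study staff will conduct structured telephone interviews at 6 months and 12 months after the ED visit". The calls ask about late symptoms, unplanned care and "any delayed diagnoses of intracranial injury". Record review and surrogate contact come into play only once three call attempts have failed.
- **Safety aim.** Table 2 sets the objective "Monitor for adverse outcomes from missed injuries in biomarker-guided arm" and lists delayed diagnoses among its measures. Safety analysis compares, between arms, the rate of delayed diagnosis of significant intracranial findings needing intervention.
- **Oversight.** Study design and methods states that no DSMB was required. An independent Medical Monitor reviews cumulative safety data each quarter and at interim analyses, and may recommend early termination "if predefined neurologic severe adverse events thresholds are exceeded (Table 3").

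**The concern.** The intervention works by letting clinicians forgo a CT. The harm particular to it is an intracranial injury that goes unrecognised because no CT was done, and the article names that harm as its safety objective and endpoint. The adverse event window, however, closes when the patient leaves hospital. For someone discharged from the ED without imaging, it closes before a delayed diagnosis is possible.

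What is at stake is the timeliness of oversight, not the primary endpoint. Without a DSMB, the Medical Monitor is the only independent safety reviewer the article describes, and that role's trigger is built on neurologic serious events. If the events that matter most enter the data months later, several reviews can pass, and recruitment can continue, before the Monitor sees them.

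**Working it through.** The article gives no figure on this point to reproduce. The check sets its statements side by side and then gives a sense of scale.

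**1. Does the window cover the endpoint?**

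| Step | What is stated | Where |
|---|---|---|
| Endpoint | Delayed diagnosis requiring intervention | Safety analysis; Table 2 |
| Adverse event window | Ends at hospital discharge | Safety monitoring; Table 3 (t3 only) |
| First planned contact afterwards | 6 months after the ED visit | Post-discharge follow-up |
| Record review | Only after three failed calls | Post-discharge follow-up |

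A patient who goes home without CT has had no imaging diagnosis by discharge, so any later diagnosis falls after the window has closed. For these patients the endpoint and the window do not overlap. Deterioration during an ED stay or admission is covered.

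**2. Does expedited reporting reach these events?** Serious events are a subset of adverse events, and adverse events are recorded only to discharge. The 24-hour clause has no end date of its own, but nothing scheduled before the 6-month call would bring a post-discharge event to the coordinators' notice. The definition names a prolonged stay but not a new admission, so a return admission after ED discharge is not plainly included.

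**3. How late would the Monitor learn of an event?** For a patient discharged from the ED, the gap to first planned contact is about 6 months. At one review every 3 months, 6 / 3 = 2 quarterly reviews. An event soon after discharge waits nearly the whole gap; a later one waits less.

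**4. Scale.** Inputs from Sample size justification: 70% CT use at baseline, a 15% reduction and 150 evaluable patients per arm. The article does not say whether 15% is absolute or relative.

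- Blinded arm unscanned: 150 × (1 − 0.70) = 45.
- Published arm, absolute reading: CT rate 0.70 − 0.15 = 0.55; unscanned 150 × 0.45 = 67.5; excess 67.5 − 45 = 22.5, about 23.
- Published arm, relative reading: CT rate 0.70 × 0.85 = 0.595; unscanned 150 × 0.405 = 60.75; excess 60.75 − 45 = 15.75, about 16.

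At the enrolment maximum of 175 per arm, the excess is 175 × 0.15 = 26 (absolute) or 175 × 0.105 = 18 (relative). All of these count unscanned patients. The article does not say what share would be discharged or how many would have an injury.

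**5. The threshold citation.** The Monitor's thresholds are referred to Table 3. That table is the SPIRIT schedule of assessments and contains no thresholds.

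**The case against.** The other side has real points.

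- **The events are collected.** The 6- and 12-month calls ask about delayed diagnoses, ED visits and readmissions in both arms, with records and surrogates as backup. This stands: the final between-arm comparison will have these data.
- **Cumulative safety data may include the calls.** The term is not limited to events before discharge. A reader might infer that the Monitor never sees post-discharge events; the text does not support that. It supports only that they fall outside the adverse event definition and arrive late.
- **Blinded adjudication.** A reader might infer from the single t3 mark in Table 3 that post-discharge events go unadjudicated. Study design and methods says outcome adjudicators are masked, with no time limit, and the follow-up columns of Table 3 show nothing beyond the phone calls themselves. A blank cell there proves little.
- **Interim bias.** A reader might infer that interim safety comparisons are biased towards no difference. The article describes no interim comparison of safety between arms, only a Monitor reviewing data against thresholds.
- **Few events are expected.** Suppose the extra unscanned patients all test negative (an assumption). With the article's general NPV of above 99%, at most 22.5 × 0.01 = 0.2 of them would be CT-positive. With the 96.5% that Table 1 gives for the whole-blood test, it is 22.5 × 0.035 = 0.8. Fewer would need intervention. This stands as a statement about numbers. It does not argue for learning of them late: when few events are expected, each one carries weight in a threshold review.
- **Minimal risk and condensed text.** The study was judged minimal risk, and an article shortens its protocol. But the window is stated outright and repeated in the schedule, so it is a rule the article fixes. Whether CT can be reduced safely is what the trial sets out to test.

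**Conclusion.** The mismatch is real. The adverse event window does not cover the trial's own delayed-diagnosis endpoint for patients sent home without CT. Such events lie outside the adverse event definition and the 24-hour rule, and would generally reach the Medical Monitor up to about 6 months, or about two quarterly reviews, late. They remain available for the final comparison, and the primary endpoint is unaffected.

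The scale of about 16 to 23 more unscanned patients per 150 rests on the planned effect being achieved and on how the 15% is read. It is not a count of discharged patients, missed injuries or harms, none of which the article allows one to derive. The statement about delay assumes that the 6-month call is the first routine source of post-discharge information, as the article describes. An event that came to the coordinators' notice by chance could be known sooner.

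**What to change.** 1. Extend the adverse event and serious event window past discharge, in Safety monitoring and in Table 3.
2. Add one fixed early electronic-record review for every randomised patient in both arms, for example at about 30 days. The exact day is a choice for the sponsor. Existing coordinators can use the record-review procedure already set out under Post-discharge follow-up.
3. Count new admissions, delayed intracranial diagnoses and deaths found there as reportable events.
4. Send them to the blinded adjudicator and to the Medical Monitor. State that call data go the same way, and add the entries at t4 and t5 in Table 3.
5. As a minor editorial matter, correct the Table 3 citation so that it points to where the neurologic serious event thresholds are held.

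The cost is some protocol wording and one short chart review per patient, up to 350 in all. No clinical care changes. Events treated at other hospitals may still be missed until the calls, so the early review shortens the delay without removing it.

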### Safety analysis

Safety analysis will be evaluated by assessing the rate of delayed diagnosis of significant intracranial findings that require intervention and will be compared between the two groups using a Pearson’s Chi-squared test. The time to CT head imaging will also be compared between two groups using a two-sample *t*-test or Wilcoxon rank sum test depending on the normality assumption.

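### The serious-adverse-event definition counts a prolonged hospital stay but not a first admission or readmission, so some harm from a missed injury escapes 24 h reporting

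*Protocol article*

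**What the plan says.** The Safety monitoring section sets two tiers. The first is recording: "All adverse events from consent through hospital discharge–neurological deterioration, unplanned neurosurgical intervention, escalation of care, or death–are recorded prospectively". The second is a 24 h report to the IRB and sponsor, limited to "serious AEs (death, life-threatening event, or event resulting in prolonged hospitalization". The second list has three items and is worded as complete, with nothing to mark it as examples.

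The section on post-randomization in-hospital assessment follows every participant through the ED stay, and through a hospital stay only for those who are admitted. The Secondary analyses section compares rates of discharge, floor admission and ICU admission, so discharge from the ED is an expected outcome.

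The trial names its own hazard. Table 2 has the objective "Monitor for adverse outcomes from missed injuries in biomarker-guided arm", and the Safety analysis section plans to compare the arms by "assessing the rate of delayed diagnosis of significant intracranial findings that require intervention".

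After discharge, telephone interviews at 6 and 12 months ask about "unplanned healthcare utilization (ED visits, hospital readmissions, outpatient imaging), and any delayed diagnoses of intracranial injury". No expedited route is described for what they find. The Study design and methods section states that no data safety and monitoring board was needed. A Medical Monitor reviews cumulative safety data quarterly and at each interim analysis.

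**The concern.** The hospitalization criterion is written for patients who already occupy a bed, since only an existing stay can be prolonged. In an ED trial, a lesion missed after a deferred CT can instead show itself as an admission that would not otherwise have happened, either from the ED or on a return visit. On a plain reading neither is a prolongation. Unless the event is fatal or life-threatening, it is not serious under this definition and the 24 h rule does not apply.

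At stake is the speed of notification. With no safety board, the 24 h report to the IRB and sponsor is the only fast channel the article describes. The other routes are quarterly or interim review and calls at 6 and 12 months.

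**Working it through.** No stated figure has to be reproduced. The check sets the definition against the events it should catch.

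| Non-fatal event, not life-threatening | Inside the recording period? | Serious under the three items? |
|---|---|---|
| Deterioration in an admitted patient that lengthens the stay | Yes | Yes |
| The same deterioration in the ED, leading to a first admission | Yes | No on a plain reading; arguable on a broad one |
| Unplanned neurosurgery in hospital | Yes, listed by name | Only if it also lengthens the stay |
| Return after discharge, delayed diagnosis, new admission | No, recording stops at hospital discharge | No, this is a new stay |
| Lasting disability found at 6 or 12 months | No | No |

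1. The first two rows differ only in whether the patient had already been admitted, yet that decides whether the event is reported within 24 h. This gap lies inside the recording period, so it does not depend on how long events are recorded.
2. The items "unplanned neurosurgical intervention, escalation of care" stand in the recording list and not in the serious list. Neurosurgery would often qualify anyway, as life-threatening or as lengthening a stay, so that gap is narrower than the one for admissions.
3. The last two rows have two causes: the definition, and a recording period that closes at discharge. Table 3 likewise marks adverse event monitoring only in the post-allocation column. Widening the definition alone would not bring these events in.

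A rough scale for how many lesions the test might not flag in the published arm:

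- Arm size: 350 / 2 = 175 (maximum enrolment, 1:1).
- Sensitivity s: 96.5% (whole-blood test, Table 1) to 97.6% (Introduction).
- CT-positive prevalence p: assumed 5% to 15%. The Introduction's figure of up to 90% negative scans implies about 10% or more among those scanned.
- Expected number with a positive CT and a non-elevated test = 175 × p × (1 − s). Chance of at least one = 1 − [1 − p(1 − s)]^175.

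Results:

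- p = 10%, s = 96.5%: 175 × 0.10 × 0.035 = 0.61; chance of at least one 46%.
- Low end, p = 5%, s = 97.6%: 175 × 0.05 × 0.024 = 0.21; chance 19%.
- High end, p = 15%, s = 96.5%: 175 × 0.15 × 0.035 = 0.92; chance 60%.

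These figures show only that such patients would be few. They are not forecasts of harm. Some of these patients would be scanned anyway, because the decision stays with the provider and patient, and not every lesion leads to an event. Nor do they count lesions left unscanned for other reasons in either arm.

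**The case against.** The strongest reply is that seriousness controls only the 24 h report. All adverse events up to discharge are recorded, including neurosurgery, escalation of care and neurological deterioration. The Medical Monitor sees cumulative data, not serious events alone. The Monitor may recommend changes or termination "if predefined neurologic severe adverse events thresholds are exceeded (Table 3"), which speaks of severe rather than serious events; Table 3 as printed is a schedule and gives no threshold values. Delayed diagnoses needing intervention are compared between arms whatever their classification, and the telephone calls collect readmissions. All of this stands. A reader might infer that the narrow list would remove most of the safety signal, but the documents do not support that.

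Second, the article is not consistent about hospitalization. The blinded-arm procedures use the word for every patient, and recording runs to hospital discharge for all. On that usage, turning an expected discharge into an admission could count as prolonging a stay. The in-hospital assessment section uses the word more narrowly. The text is therefore ambiguous for a first admission from the ED, which is itself a reason to settle it in words. The broad reading does not rescue a readmission after discharge.

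Third, the full protocol may hold a longer definition that the article condenses. That is possible, but the printed list reads as complete, and it is the rule a reader has.

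Fourth, admission is an ordinary disposition in a trauma cohort, so adding every admission would flood the reports. That is right, and the fix needs a qualifier.

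**Conclusion.** The point holds as a stated rule drawn too narrowly for an ED population. The clearest gaps are a first admission from the ED and a readmission after discharge. Persistent disability is also absent from the list, and unplanned neurosurgery is covered only when another criterion applies. The consequence is delayed notification to the IRB and sponsor of a small number of events that bear directly on the trial's safety question. Nothing suggests lost data or a biased comparison.

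The conclusion assumes that the article's list is the operative definition and that some participants are not admitted. It does not need most of them to be outpatients. A reader might infer that from the ED setting, but the article gives no discharge rate, and the site is a level I trauma center.

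Nor can the planning rates be used to size the gap. At 70% and 55% scanned with 150 per arm, 150 × 0.30 = 45 and 150 × 0.45 = 67.5 patients would be unscanned. The Introduction's figure of fewer than 1% needing neurosurgery gives at most 300 × 0.01 = 3 cases. Neither figure counts lesions missed after a deferred scan.

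**What to change.** Extend the definition, identically in both arms and with the same 24 h reporting, so that a serious adverse event also includes one that results in:

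- initial or renewed hospital admission, excluding admission for the index injury as found at enrolment;
- unplanned neurosurgical intervention; or
- persistent disability.

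In the same edit, reconcile the definition with the recording period that ends at hospital discharge. Readmissions and delayed intracranial diagnoses after discharge should be reportable from the time the study team learns of them, including through the 6- and 12-month calls. If the full protocol already says this, it is enough to align the article with it.

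The cost is a short protocol amendment, a change to the adverse event form and a few more expedited reports. The index-injury exclusion keeps routine admissions out. For disability first found at a late call, 24 h reporting adds little beyond a consistent rule.

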### Rationale for early biomarker use

GFAP and UCH-L1 enter the bloodstream minutes to hours after mild traumatic brain injury and, when measured on the handheld i-STAT TBI cartridge, yield quantitative results in ≈ 15 min. Large prospective cohorts and FDA-clearance data show that the combined assay has ≥96% sensitivity and >99% NPV for predicting CT-positive intracranial injury within 24 h of trauma, permitting safe imaging deferral in biomarker non-elevated cases (12, 19, 24). Because standard decision rules (e.g., the Canadian CT Head Rule, institutional common practices) still lead to CT scanning in up to 70% of emergency-department patients, embedding real-time GFAP and UCH-L1 testing into the initial evaluation offers an evidence-based, objective tool to reduce unnecessary radiation, crowding, and cost while maintaining diagnostic safety (25).

